## 18.2 Retention

### 18.21 Strategies

Once an apprentice is enrolled in the TDTP, the Training Program Coordinator will make every reasonable effort to develop a BCM plan for each apprentice that will be directed at all the existing or potential barriers that may threaten their program attendance or completion.

### 18.22 Withdrawal

Apprentices may choose to withdraw from the study for any reason at any time without any adverse consequences on their TDTP enrollment. For those apprentices who withdraw for any reason, all data collected up to the time of their withdrawal will be included in the final analysis. Deviations from the study protocol (which do not result in withdrawal) or loss-to-follow-up for any reason will not be considered reasons for withdrawal from the study.

# 19 Data management

All data collected using the Distress Thermometer screening tool (Section 18.11) will be encrypted and stored in a Microsoft Azure SQL Database. Differential backups of the database will be performed automatically once every 24 hours, with full backups being performed automatically once every week. Backups are replicated to three separate Azure data centers within the same region, ensuring that data will not be lost if one data center becomes unavailable. All instances where personal health information is created, viewed, or updated will be recorded in an electronic audit trail that identifies the person to whom the information relates, the user accessing the information, the type of information, and the date and time that the information was accessed. Data access by users of the tool is regulated by privileges associated with their user identification and password. The data is password-protected and will only be accessible by apprentices during their 12-week TDTP after which time they will no longer be able to access the screening tool. In addition, the TDTP Training Coordinator will have password-protected access to all apprentices’ data for their 12-week TDTP after which time they will no longer be able to access those apprentices’ data. The MH&A counsellors will have password-protected access to a limited data set that includes only those apprentices who have had a clinical referral. Again, access will be limited to the 12-week TDTP.

All demographic data (Section 18.11) will be entered electronically by apprentices into REDCap through a secure survey link that will be sent by email upon registration in the Distress Thermometer screening tool. A unique study number will be assigned to each apprentice in REDCap. This unique study number, along with the patient’s name (first, middle, last), Ontario Health Insurance Plan number, date of birth, and unique electronic health record system number (if applicable) will be stored in a password-protected EXCEL computer file. This study EXCEL file will be stored in a dedicated, password-protected electronic shared drive located on the Royal Victoria Regional Health Centre Personal Health Information Protection Act (PHIPA)-compliant servers. This EXCEL file will permit linkage to the electronic case report form to enable study personnel to record outcome data over the study period for a participant. Real-time data quality rules will be implemented in REDCap that will display warning pop-up messages whenever the rules are violated during data entry. These quality rules will minimize missing values in required fields; prevent incorrect data type entry and out of range data entry; identify outliers for numerical fields; and prevent invalid data entry into multiple choice fields. The data quality rules will also be available to be executed at any time by a study monitor or study personnel. All electronic case report form entries and edits are associated with an electronic audit trail that identifies the user, date and time of entry, and entry type. The type of activity that study personnel may undertake in REDCap is regulated by privileges associated with their user identification and password. Incremental data back-ups of REDCap are routinely performed twice a day, with off-site storage of the backed-up files done on a monthly basis.

All study-specific data that is survey-based (Section 18.13 and 18.13a) will be completed by apprentices during orientation or after the completion of the TDTP. Secure links for each of the surveys will be sent by email to each apprentice. All survey responses will be stored in REDCap using the previously assigned unique identifier. Study-specific data related to clinical outcomes will be extracted by study personnel from the electronic medical record system (dates and times of Mental Health and/or Addictions healthcare visits) and stored in REDCap. All other study-specific outcome data related to program completion and employment (Section 18.13) will be collected by study personnel who will enter the data in REDCap.

All study data will be archived in REDCap for 10 years and subsequently permanently destroyed.

# 20 Statistical methods

## 20.1 Outcomes

The intervention arms (ICM^10^ (Distress Thermometer screening tool), ICM^01^ (MH&A fit-for-purpose program), ICM^11^ (Both Distress Thermometer and MH&A) will be compared against the active comparator (BCM) for all primary and secondary analyses where applicable. All inferential and descriptive analyses will be at the individual level after accounting for the effects of clustering (id and cohort).

### 20.11 Primary

#### 20.11a Program attendance

We will use a 3-level hierarchical design to model the program attendance data where the observation for each day (Level 1) will be coded as binary; attendance (=1) versus absence (=0). Level 1 observations are clustered within individual apprentices (Level 2) , which are nested within cohorts (Level 3). We will analyse the outcome data using multi-level, mixed-effects logistic regression analysis with fixed effects estimated for the variance in the intercepts of both apprentice and cohort levels. The interventions (Distress thermometer and MH&A) will be included as well as a variable for their interaction effect. We will also include time period (year-quarter) and an interaction term between the time period and each intervention (Distress thermometer and MH&A). A sensitivity analysis will be conducted to compare this baseline model with an extended model that includes any baseline demographic or clinical variables that appear to be unbalanced at Level 1. The models will be compared using the likelihood-ratio comparison test for superiority. Post-regression analyses using *margins* command will be used to estimate difference in program attendance between treatment groups.

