# 12 Outcomes

## 12.1 Primary outcome measures

### 12.11 Program attendance

Difference in proportion of absence-free program days (AFDs) at 12 weeks from the start date of the TDTP, where ***absence-free days are defined by the cumulative number of days of program attendance during the 12-week study period.*** The potential number of AFDs for each apprentice is the cumulative number of program days that the apprentice is alive during the 12-week TDTP, with a maximum of 48 days (=12 weeks x 4 days/week). A day is defined as an 8–10-hour work-day during the TDTP from Monday to Thursday. An apprentice is considered to have attended a work-day as long as the Case Manager or their construction supervisor documents their attendance.

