### 12.12 Program completion

Difference in proportion of drop-outs at 12 weeks from start date of TDTP, where ***a drop-out is defined as an apprentice who fulfils any of the following criteria:***

- Has missed more than 50% of training days, or
- Who has elected to leave the program for reasons other than taking another job or returning to school

The proportion of drop-outs is defined as the ratio between the cumulative number of apprentices who meet the criteria for drop-out relative to the cumulative number of apprentices enrolled in the TDTP.

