## 14.1 Difference in proportion of AFDs

The sample size is fixed at approximately 448 individuals. We anticipate that the first few cohorts will be asked to pilot the screening tool, potentially removing up to 50 apprentices from the final sample size. We will use a fixed sample size of 400 apprentices, divided equally between Sudbury and Barrie sites. The expected cohort sizes will range from 6 to 10 apprentices, resulting in 20 to 34 cohorts per site. We will use a 3-level hierarchical design to model differences in proportion of AFDs where the daily attendance (Level 1) will be coded as binary; 0 for absence and 1 for attendance. Level 1 observations are clustered within individual apprentices (Level 2), which are nested within individual cohorts (Level 3). The sites (Sudbury and Barrie) and start date of cohort enrollment (q1 (January-March); q2 (April-June); q3 (July-Sept); q4 (Oct-Dec) and year) will be included as confounding variables in Level 1 and will not enter into the power calculations. Using this design, we performed a sensitivity analysis to determine the power to observe different primary outcome effect sizes with an $\alpha$-level 0.05**.**  As can be seen in the following table, even small differences in attendance (5% difference in proportions of AFDs) would still be detected with power ≥ 80% as long as the Level 2 inter-cluster correlation ≤ 0.125, a very reasonable assumption as there is no reason to believe that these apprentices’ attendance behaviours will be highly correlated with each other (23).

|  | **Scenarios**^1^ | | | | | | | |
| --- | --- | --- | --- | --- | --- | --- | --- | --- |
| **Variables** | 1 | 2 | 3 | 4 | 5 | 6 | 7 | 8 |
| Test Significance Level, α​ | 0.05 | 0.05 | 0.05 | 0.05 | 0.05 | 0.05 | 0.05 | 0.05 |
| Mean Difference, δ = µ₁ - µ₂​ | 0.1 | 0.15 | 0.05 | 0.05 | 0.05 | 0.05 | 0.05 | 0.1 |
| Standard Deviation, σ​ | 0.1 | 0.1 | 0.1 | 0.1 | 0.1 | 0.1 | 0.15 | 0.15 |
| Level 1 Unit Correlation, ρ₁​ | 0.75 | 0.75 | 0.75 | 0.75 | 0.75 | 0.75 | 0.75 | 0.75 |
| Level 2 Unit Correlation, ρ₂​ | 0.5 | 0.5 | 0.5 | 0.25 | 0.125 | 0.05 | 0.05 | 0.05 |
| Number of Level 3 Units in Group 1, C₁​ | 15 | 15 | 15 | 15 | 15 | 15 | 15 | 15 |
| Number of Level 3 Units in Group 2, C₂​ | 15 | 15 | 15 | 15 | 15 | 15 | 15 | 15 |
| Level 3 Units per Group Ratio, C₂/C₁​ | 1 | 1 | 1 | 1 | 1 | 1 | 1 | 1 |
| Number of Level 2 Units per Level 3 Unit, K​ | 6 | 6 | 6 | 6 | 6 | 6 | 6 | 6 |

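### The day-level logistic model in section 20.11a can misstate the difference in absence-free-day proportion defined in section 12.11, because leavers contribute unbroken runs of absence that the model does not represent

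*Protocol*

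**What the plan says.** Protocol section 12.11 makes the first primary outcome a difference in proportion of absence-free program days. Its denominator is fixed: "The potential number of AFDs for each apprentice is the cumulative number of program days that the apprentice is alive during the 12-week TDTP". The section caps this count at 48. Leaving does not shorten that denominator, so a day after leaving is a day not attended. The section implies this without spelling it out.

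Leaving is an expected event. Section 12.12 includes among drop-outs an apprentice "Who has elected to leave the program for reasons other than taking another job or returning to school", and section 14.2 reports historical completion of 75-80%.

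Section 20.11a sets the analysis: "the observation for each day (Level 1) will be coded as binary; attendance (=1) versus absence (=0", with the structure "Level 1 observations are clustered within individual apprentices (Level 2) , which are nested within cohorts (Level 3". The method is "mixed-effects logistic regression analysis with fixed effects estimated for the variance in the intercepts of both apprentice and cohort levels". The model adds the two interventions, their interaction, and year-quarter with its interactions, but no term for leaving and none for serial dependence between days. The effect is then obtained as follows: "Post-regression analyses using *margins* command will be used to estimate difference in program attendance between treatment groups".

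Section 14.1 states the effect of interest on the AFD scale: "even small differences in attendance (5% difference in proportions of AFDs) would still be detected with power ≥ 80" percent.

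**The concern.** An apprentice who leaves in week 4 contributes a few weeks of mostly attended days and then an unbroken run of zeros. Apprentice-level attendance is then two-humped: stayers near the top, leavers spread from zero upward. A mixed logistic model with a single intercept per apprentice treats days as independent given that intercept. On the usual reading it also draws intercepts from one normal distribution with the same variance in every arm. Neither feature fits a mixture of stayers and leavers.

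Margins averages fitted probabilities over that intercept distribution. If the distribution is wrong, the averaged difference need not equal the difference in mean AFD proportion.

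What is at stake is the reported effect size for the first primary outcome. The direction of the error depends on whether an intervention works by keeping people in the program or by improving attendance while they are in it, and this is unknown in advance. If days after leaving were left blank instead, the model would measure attendance while enrolled, which is a different outcome from section 12.11.

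**Working it through.** **Inputs from the protocol.** 48 days per apprentice and a denominator of all program days alive (12.11); daily 0/1 coding, apprentice and cohort intercepts, margins (20.11a); completion 75-80%, hence 20-25% non-completion (14.2); AFD difference of interest 0.05 and alpha 0.05 (14.1).

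**Inputs assumed, because the protocol gives none.** Stayers attend 85-95% of days; leavers attend at the same rate until they leave; leaving time is uniform; apprentices vary with a logit SD of 0.5-1.0 or a beta distribution; all non-completers are leavers; intercepts are normal with common variance; margins are averaged over them.

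**1. The plan's own figure.** Section 14.1, scenario 5: f = 1 + (10 - 1) x 0.75 + 10 x (6 - 1) x 0.125 = 14.0. SE = sqrt(2 x 0.1² x 14.0 / (15 x 6 x 10)) = 0.01764. Power = Phi(0.05/0.01764 - 1.96) = 80.9%, as stated. This calculation concerns a difference in means with an SD. It says nothing about how the logistic model behaves.

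**2. True AFD difference.** With stayer attendance p, leaving proportion q and leaving day T uniform on 0 to 47 (mean 23.5), mean AFD proportion = p x [1 - q x (1 - 23.5/48)] = p x (1 - 0.5104q).
- Leaving 20% to 10%, p = 0.95: 0.8530 to 0.9015, difference 4.85 points.
- Stayers 90% to 95%, q = 0.20: 0.05 x 0.8979 = 4.49 points.

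**3. What the model reports.** Days attended given the intercept are Binomial(48, expit(a + b x arm + u)), with u normal and its SD s common to the arms. The parameters a, b and s maximise the large-sample likelihood. The margins difference is the mean of expit(a + b + u) minus the mean of expit(a + u). With beta-distributed apprentice attendance (concentration 20 and 40):

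| Control to intervention | True (points) | Model (points) | Error |
|---|---|---|---|
| Leaving 20% to 10%, stayers 95% | 4.85 | 3.4-3.5 | -30% to -29% |
| Leaving 25% to 15%, stayers 92% | 4.70 | 3.7 | -22% |
| Stayers 90% to 95%, leaving 20% | 4.49 | 7.7-7.9 | +72% to +75% |
| Stayers 88% to 93%, leaving 25% | 4.4 | 6.8-7.0 | +57% to +59% |
| Stayers 90% to 93%, leaving 20% to 15% | 5.1 | 6.1 | +19% to +21% |
| Stayers 90% to 92%, leaving 20% to 13% | 5.1 | 5.2-5.3 | +3% to +4% |
| Stayers 90% to 91.5%, leaving 20% to 12% | 5.1 | 4.9 | -4% to -3% |
| Identical arms | 0 | 0 | none |

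Widening the concentration to 5-50 moves the three joint-improvement rows to between -5% and +24%.

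**4. Varying the assumptions.** With normal heterogeneity on the logit scale, leaving over days 1-47 or 1-24, and the true difference held at 0.05:
- Effect only through leaving: -13% to -31%, with most settings between -20% and -30%.
- Effect only through attendance while enrolled (stayers at 85-90%): +14% to +85%. For a smaller true difference of about 0.02 with 95% attendance, +65% to +159%.
- Both effects together (true differences 0.03-0.09): +1% to +14%.
- No leaving at all: 0%.

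A three-level fit with a cohort intercept and cohorts of 8 gave -22% (leaving), +42% (attendance) and +9% (both). If margins sets the intercepts to zero instead of averaging over them, the errors run from about -51% to +113%.

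**5. Source of the error.** Letting the intercept variance differ by arm brings the first row to 5.0-5.1 against 4.85 and the third to about 5.1 against 4.49. Much of the error therefore comes from the common variance. The mean of days attended/48 per arm involves no intercept distribution, so its difference equals the true AFD difference whatever the leaving pattern.

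**The case against.** Several points on the other side are sound. The protocol gives no stayer attendance rate, leaving-time distribution or between-apprentice spread, so no percentage above can be derived from it. Normality of the intercepts and the margins option are also unstated. The wording about fixed effects for intercept variance is unclear, and an analysis plan might settle it. Nor is all non-completion leaving: section 12.12 also counts apprentices who miss more than half the days. On the other hand, those who leave for a job or school are not drop-outs yet still produce runs of zeros. The share of apprentices with such runs is therefore unknown. The hypotheses in section 6.1 expect absenteeism and drop-out both to fall, and there the two errors largely offset.

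A reader might infer three stronger things.
- **That the estimate is off by a fixed, known percentage.** It is not. The figures are illustrations and not bounds.
- **That the test has inflated type I error.** With identical arms the margins difference is zero. Rejection at equal AFD proportions needs opposing effects. With stayers rising from 90% to 95% while leaving rises from 15% to 24.4%, the true difference is about 0.1 points and the model gives 4.3-4.4. This is an extreme case in which the arms differ on both behaviours. A milder offset (leaving 20% against 25%) gives only 1.4 points.
- **That the power table is wrong.** It reproduces.

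The mismatch itself stands. The denominator and the day-level model are both fixed in the protocol, and reading the intercepts as properly random does not remove the problem, since every calculation above already does so. The comparisons in section 7.1 set each single intervention against usual case management, so an effect through one channel is plausible.

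**Conclusion.** The concern holds as a conditional one. The analysis in section 20.11a does not in general estimate the quantity in section 12.11 when some apprentices leave. Under the stated assumptions, the error is typically -20% to -30% for an effect on leaving alone, roughly +15% to +85% for an effect on attendance while enrolled alone, and about -5% to +25% when both improve. It is zero for identical arms. Against the 5-point difference considered in section 14.1, single-channel errors amount to roughly 1 to 4 points, which would matter for interpretation. The plan should be corrected on this point. The concern does not show that the test is invalid or that the trial is wrongly sized.

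**What to change.** In section 20.11a, make the primary estimate one value per apprentice: days attended divided by program days alive, stating that days after leaving are coded 0. Analyse it by linear (identity-link) or fractional-logit regression with the same design terms. Account for cohort clustering by a cohort random intercept or by cohort-robust standard errors with small-sample correction. Report the difference in AFD proportion directly. Keep the day-level mixed logistic model as a supportive analysis of attendance over time.

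The cost is wording in the protocol and any analysis plan; the data collected do not change. The downside is that day-level modelling is no longer primary.

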#### 18.13a Foundational skills

Complete essential skills self-assessment for the trades questionnaire (28). There are 9 foundational skills identified in the questionnaire, each containing statements that require the apprentice to answer *yes, somewhat or no.*  For any skills sub-domain in which the apprentice answers *somewhat* and/or *no* in less than 5 statements, the apprentice is considered to possess a *strength* in that foundational skill. A cumulative score of the number of foundational skills that each apprentice possesses (out of 9) will be calculated and used as a baseline variable. Each apprentice will be asked to complete this survey as part of the routine orientation process. The survey link will be provided to each apprentice and all results will be stored in REDCap using a unique identifier number.

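### The extended attendance model takes its covariates from apparent imbalance at the wrong level, is compared with the baseline model by fit, and the plan does not name the model that supplies the treatment difference

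*Protocol*

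**What the plan says.** Section 20.11a sets out the levels first, with each day scored as attended or absent: "We will use a 3-level hierarchical design to model the program attendance data where the observation for each day (Level 1) will be coded as". Days lie within apprentices (Level 2), and apprentices within cohorts (Level 3). The baseline model holds both interventions, their interaction, and calendar terms: "We will also include time period (year-quarter) and an interaction term between the time period and each intervention".

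A second model follows: "A sensitivity analysis will be conducted to compare this baseline model with an extended model". The protocol describes that second model as an "extended model that includes any baseline demographic or clinical variables that appear to be unbalanced at Level 1". No list and no threshold for imbalance is given. Next comes "The models will be compared using the likelihood-ratio comparison test for superiority", without saying what follows from the result. Finally, the Stata margins "command will be used to estimate difference in program attendance between treatment groups", with no statement of which model it is run on.

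Section 20.12a uses the same wording for time to access mental health and addictions services. Sections 20.11b and 20.11c (completion and employment) have no such step. Section 17 says data analysts are not masked. Section 18.13a has each apprentice complete the skills survey at orientation and says a score out of 9 "will be calculated and used as a baseline variable". No model in Section 20 names that score.

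**The concern.** Four features of this text are weak.

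- **Which estimate is primary is not closed off.** A sensitivity analysis does not normally test two models for superiority. Here the test comes before the effect is estimated, and the model for that estimate is not named. An unmasked analyst could read the sequence as permission to report the better-fitting model.
- **Imbalance is the wrong criterion.** In a randomised comparison, a covariate earns its place by predicting attendance. A variable that differs by chance but is unrelated to attendance adds nothing. A strong predictor that happens to be balanced is left out.
- **A likelihood-ratio test answers a different question.** It says whether the covariates improve fit, not which treatment estimate should be primary.
- **The level is wrong.** Demographic and clinical baseline variables belong to the apprentice (Level 2) and do not vary by day (Level 1).

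At stake is a firmly fixed estimate for one of three primary outcomes, and precision that pre-specified adjustment would give at little cost. Section 14.1 reaches 80% power for a 5-point difference only if the Level 2 correlation is at most 0.125, so a few points of power matter.

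**Working it through.** **1. Reproduce the plan's power.** Inputs from the Section 14.1 table, scenario 5: difference 0.05, SD 0.1, Level 1 correlation r1 = 0.75, Level 2 correlation r2 = 0.125, C = 15 cohorts per group, K = 6 apprentices, M = 10 days, alpha 0.05 (sidedness is not stated; two-sided reproduces the table).

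- Design factor: f = 1 + (M-1)·r1 + M·(K-1)·r2 = 1 + 6.75 + 6.25 = 14.0
- SE = SD·√(2f/(C·K·M)) = 0.1·√(28/900) = 0.01764
- Power = Φ(0.05/0.01764 − 1.96) = Φ(0.875) = 80.9%, as stated

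All eight scenarios reproduce within 2 points: 96.0, 100.0, 45.8, 65.4, 80.9, 91.2, 59.8 and 99.3%, against the stated 95.9, 99, 45.7, 65.4, 80.9, 91.1, 59.8 and 99%. The stated power assumes no apprentice covariates, so this step does not make it wrong.

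**2. Add fixed apprentice-level adjustment.** If covariates explain a share R² of the between-apprentice variance (r1 − r2 = 0.625), f falls by R²·M·(r1 − r2) = 6.25·R². For R² = 0.10, f = 13.375, SE = 0.01724 and power = 82.6%. For R² = 0.50, f = 10.875, SE = 0.01555 and power = 89.6%. The protocol gives no R², so the range is an assumption:

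| Level 2 correlation | R² = 0 | 10% | 20% | 30% | 50% |
|---|---|---|---|---|---|
| 0.25 | 65.4 | 66.5 | 67.6 | 68.8 | 71.1 |
| 0.125 (scenario 5) | 80.9 | 82.6 | 84.4 | 86.1 | 89.6 |
| 0.05 | 91.2 | 93.0 | 94.6 | 96.0 | 98.3 |

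**3. What selection by imbalance recovers.** A simulation of apprentice-level means used assumed inputs: 15 against 15 cohorts of 6, ten baseline variables of which three are prognostic, imbalance flagged per apprentice, then a likelihood-ratio test at 0.05. At least one variable looked unbalanced in about 40% of trials with a p<0.05 flag and about 89% with p<0.20. The test then favoured the extended model in roughly 12-16% and 36-51% of trials. SD of the estimated effect at R² = 30%, no true effect:

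| Flag | Baseline model | Imbalance plus likelihood ratio | Fixed set |
|---|---|---|---|
| p<0.05 | 0.200 | 0.197 | 0.185 |
| p<0.20 | 0.196 | 0.187 | 0.179 |

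The variance reduction is 1 − (0.197/0.200)² = 3% under selection against 1 − (0.185/0.200)² = 14% with the fixed set. At p<0.20 it is 9% against 17%.

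A second simulation (40 cohorts of 10, intracluster correlation 0.05, 12 covariates, R² from 0.1 to 0.4) agrees in direction. Power was 75.8-80.4% under per-apprentice imbalance plus the test, against 78.2-93.6% with all 12 fixed; at R² = 0.2 it was 78.1% against 84.6%.

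**4. Type I error.** In the first simulation, letting the test choose the model gave 3.4-4.4%, against 3.7-4.4% for the baseline model. Reporting whichever model had the larger test statistic gave 4.2-5.3%. In the second, the selected model gave 2.8-3.9%. Selection does not inflate the false-positive rate.

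Both simulations are linear approximations to the planned logistic model. In the logistic model the gain shows in power and in the margins difference, not as a smaller standard error for the conditional log odds ratio.

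**The case against.** **The extended model is labelled a sensitivity analysis.** This stands. The baseline model is specified and on its face primary, and nothing says the winner of the likelihood-ratio test replaces it. A reader might infer that the data decide which estimate counts. The text leaves that open as a risk; it does not state it as a rule.

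**Level 1 may be a loose label.** This also stands in part. A reader might infer that balance will be tested on day records. With 48 identical rows per apprentice, a 5% test would then flag a truly balanced variable with probability 2(1 − Φ(1.96/√48)) = 0.78. The protocol does not support that reading: Section 20.1 puts descriptive and inferential analyses at the individual level after allowing for clustering by apprentice and cohort, and no test on day rows is prescribed. Section 14.1 likewise places site and start date at Level 1. The label is wrong and needs correcting, but the 78% is not a consequence of the plan.

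**Two models will sometimes disagree.** In the second simulation they differed on significance in 4-7% of trials when balance was judged per apprentice. That is what any sensitivity analysis can show, and it would also be true after the fix. It is not harm in itself.

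**An unadjusted primary analysis is valid, and covariate lists are often left to the SAP.** True. But the protocol does fix a selection rule here, and it is a poor one. Section 18.13a's remark about the skills score does not promise adjustment; it may mean description only.

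**The covariates may not exist in control cohorts.** This limits the remedy. Section 18.11 lists demographics as Distress Thermometer data, Section 19 sends the demographic link on registration in that tool, and Sections 15 and 16.3 describe consent only for cohorts allocated to it. The second simulation assumed all covariates in both arms.

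**Conclusion.** The point holds as a correction worth making, not as an error that invalidates the analysis. Sections 20.11a and 20.12a choose covariates by apparent imbalance at the wrong level, compare models by fit with no stated consequence, and do not name the model behind the treatment difference. The false-positive rate is not raised and the stated power stands. What is lost is precision: in scenario 5, about 2 to 9 points of power for R² between 10% and 50%. The gain is smaller at a Level 2 correlation of 0.25 (about 1 to 6 points). These figures rest on an assumed R² and on prognostic covariates being available in every cohort. A claim that most of the available power is thrown away would go beyond what the protocol supports.

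**What to change.** In Sections 20.11a and 20.12a:

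- Name one primary model and state that margins is run on it.
- Include the planned intervention and period terms plus a short pre-specified set of apprentice-level covariates collected in all cohorts. The foundational skills score qualifies as described in Section 18.13a. Add age, gender, education and prior mental health or substance use disorder only if control cohorts supply them too.
- Code the Rather not say response (offered for all variables in Section 18.11) as its own category, so that nobody is dropped and all models use the same apprentices.
- Report the model without these covariates as the sensitivity analysis.
- Delete the imbalance criterion and the likelihood-ratio comparison, and replace Level 1 with apprentice level (Level 2) in that sentence.

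The cost is wording and extra parameters. The skills score alone adds one. The full list, with Section 18.11 categories and the extra response level, could add up to 1 + 2 + 3 + 5 + 2 + 2 = 15 (score, age, gender, education, mental health, substance use). With 40 to 68 cohorts the list should therefore stay short, for example by collapsing education. This matters most in Section 20.12a, where only referred apprentices contribute data and the protocol gives no expected number of referrals.
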